##### Missing Data

Missing outcome data will be handled using multiple imputation by chained equations (MICE, *mice* package), generating 50 imputed datasets combined using Rubin’s rules. Imputation models will include all analysis variables, auxiliary variables predictive of missingness, and couple-level identifiers to respect the clustered structure. Results from imputed analyses will be reported alongside complete-case sensitivity analyses. The assumption of “missing at random” will be evaluated through pattern analysis and tested in sensitivity analyses under a “missing not at random” scenario using pattern-mixture models. All analyses will follow an intention-to-treat principle.

#### Qualitative Analysis

Qualitative data from postintervention interviews and open-ended questions will be analyzed using reflexive thematic analysis. This approach allows identification of patterns in participants’ experiences, perceived changes, and interpretations of the intervention. The analysis will involve systematic coding of transcripts, iterative development of themes, and collaborative interpretation among members of the research team.

Exploratory computational text analysis (eg, co-occurrence networks and sentiment analysis using *pysentimiento* and *syuzhet* [55-58]) may be conducted as a supplementary descriptive tool to explore linguistic patterns within the corpus but will not replace the primary thematic analysis.

### Governance

The coordinating center for this trial is the Universitat Oberta de Catalunya, led by the corresponding author. The research team includes clinical psychologists, VR developers, and data analysts. While no independent steering committee or endpoint adjudication committee is designated due to the study’s minimal-risk and noninvasive nature, weekly team meetings will ensure trial fidelity, recruitment flow, and protocol adherence. No data monitoring committee has been established for this trial, as the intervention is noninvasive, the anticipated risks are minimal, and the study duration is short, making formal safety monitoring beyond standard institutional oversight unnecessary. No interim analyses or formal stopping guidelines are planned, given the short duration of the study and the absence of anticipated serious risks. Likewise, no independent auditing procedures are planned beyond standard institutional oversight, as the trial is conducted within an academic setting and does not involve pharmacological or invasive interventions. No specific compensation arrangements for trial-related harm are foreseen, as no physical harm is expected; however, participants will be informed of their right to withdraw at any time and will be provided with appropriate support in case of discomfort.

### Ethical Considerations

This study was conducted following the principles of the 1975 Declaration of Helsinki, as revised in 1983, by the Research Ethics Committee of the Universitat Oberta de Catalunya. Only the principal investigators and authorized members of the research team will have access to the final trial dataset. This access will be strictly regulated to ensure compliance with ethical guidelines and data protection regulations. All participants will give consent to participate voluntarily in the study, and the ethics committee has already evaluated the procedure for obtaining their consent. This study received approval from the ethics committee of the university, with minutes of approval CE23-PF02. Given the noninvasive nature of the intervention, no formal adverse event monitoring is planned. However, participants may report any discomfort or emotional distress to the research team, and referrals to psychological support will be provided if necessary. No posttrial care is planned. The intervention poses minimal risk, and no compensation mechanism for trial-related harm is required.

Participants will receive financial compensation for their participation in the study. Specifically, each couple will receive €50 (US $54) upon completion of the study procedures. This compensation is intended to acknowledge participants’ time and involvement and is not contingent on performance or study outcomes.

The results of this study will be disseminated through publication in peer-reviewed journals and presentations at academic conferences and scientific meetings. Only aggregated data will be reported to ensure participant confidentiality. The full protocol, deidentified datasets, and analysis code will be available upon reasonable request to the corresponding author after trial completion and publication.

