#### Change Interview

This semistructured script interview was created to assess the changes produced throughout the therapy, the useful aspects, and the adverse effects of interventions from the client’s perspective [53]. Clients are asked about the changes they have experienced with the intervention, as well as the negative changes, if any. Questions are also asked regarding the attribution of such changes and their probability of occurrence without intervention. Its functions in this study are to identify both changes that clients are aware of (in their own words), which might go unnoticed with standardized questionnaires, and adverse effects (too often neglected in research).

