Phase 4 will be similar for the 3 conditions. In condition 1, men will have a virtual meeting with their partners (both still with the exchanged identity) outside the context in which the harassment situation occurred. The man will be asked to recount his experience related to the harassment experienced virtually to his partner, who will then be asked to respond empathetically. In condition 2, participants will also meet with their partners (maintaining the virtual identity exchange) outside the scenario in which they were and will be asked to discuss their concerns and expectations of the relationship related to gender issues. In condition 3, participants will discuss the sexual harassment they witnessed in the bar scene, while embodying their own avatar (not exchanged). This discussion will emphasize their reflections on the observed behavior and its consequences, promoting personal insights from their perspective as bystanders.

In phase 5, the sexualized female avatar will appear to perform the farewell, and the participants’ gaze will be traced. Before the end, two questions related to body belonging will be asked. Outcome assessments will be conducted immediately after the intervention (posttest) and at 3 months (follow-up).

The intervention will be discontinued for a participant if they experience severe cybersickness (eg, nausea, dizziness, and disorientation), acute psychological distress, or technical failures that compromise the integrity of the experience or data collection. Participants will be informed that they may request to stop the session at any time without providing a reason. In such cases, the session will be immediately terminated, and appropriate support will be offered if needed.

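### The article declines formal adverse event monitoring as noninvasive, yet foresees cybersickness and acute distress and states no tabulation of harms by arm

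*Protocol article*

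**What the plan says.** Ethical Considerations makes a positive decision: "Given the noninvasive nature of the intervention, no formal adverse event monitoring is planned". What stands in its place is spontaneous reporting, in that "participants may report any discomfort or emotional distress to the research team", with referral to psychological support where needed. The same paragraph concludes: "The intervention poses minimal risk, and no compensation mechanism for trial-related harm is required". Governance takes the same line: no data monitoring committee, no formal stopping guideline, and no physical harm expected.

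Other sections expect some harms.

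- Intervention Procedure gives as reasons to discontinue "severe cybersickness (eg, nausea, dizziness, and disorientation), acute psychological distress", alongside technical failures. A participant may also stop without giving a reason. On a stop, "the session will be immediately terminated, and appropriate support will be offered if needed".
- Change Interview: "Clients are asked about the changes they have experienced with the intervention, as well as the negative changes, if any". One of its functions in this study is to identify "adverse effects (too often neglected in research").

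On analysis, "Qualitative data from postintervention interviews and open-ended questions will be analyzed using reflexive thematic analysis", with optional exploratory text analysis as a supplement. The quantitative sections (Primary Analysis, Secondary Outcomes, Missing Data) name no harm outcome.

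**The concern.** Noninvasiveness is a reason to expect no procedural injury. It says little about nausea, disorientation or distress from a simulated harassment scene, which are the harms this article treats as possible. The stated reason therefore does not support the stated decision.

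The design makes the gap worth closing. Under Intervention Procedure, men in conditions 1 and 3 meet the harassment scene and men in condition 2 do not, while women are in a neutral setting in all three. The trial thus randomizes the exposure whose tolerability is in question. The events will come to staff in any case, as stopped sessions, distress reports, referrals and interview answers. Followed as printed, the plan gives no stated route from those events to a comparison of exposed and unexposed arms, or to evidence for the minimal-risk statement. Future Directions looks ahead to educational, bystander and rehabilitation use, where readers will want such a table.

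**Working it through.** The plan gives no figure on this point, so there is none to reproduce. The check has two parts.

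**1. What each data source records**

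| Source (section) | What it records | Is a harm table by arm stated? |
|---|---|---|
| Stopped sessions (Intervention Procedure) | Rule for stopping and support | No |
| Spontaneous reports and referrals (Ethical Considerations) | Distress that a participant chooses to raise | No |
| Change Interview; Qualitative Analysis | Negative changes, in the participant's words | No; thematic analysis, optional text analysis |
| Self-Assessment Manikin at the end of phase 3 (Changes in Affective Responses; Intervention Procedure) | Valence, arousal, dominance | No; a reaction to the scene |
| Fear-of-aggression item, 0 to 10 (Change in Body Ownership Illusion) | Fear felt during the session | No; a reaction to the scene |
| Communication, adjustment and flourishing scales (Secondary Outcomes) | Relational change, including aggressive communication | Relationship functioning is modelled by condition and time; not adverse events |

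The last three rows are real, structured information, and they can be compared between arms. None says whether a session was stopped, why, or whether a referral followed.

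**2. What a table could show**

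Inputs: 90 couples, 30 per condition (Sample), one man per couple. That gives 30 men per arm, 2 × 30 = 60 men in conditions 1 and 3, and 90 men in all. Men from different couples are treated as independent. It is assumed that all of them start a session and that every event is logged.

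With zero events, the exact (Clopper-Pearson) two-sided 95% upper limit is 1 − 0.025^(1/n):

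- n = 30: 1 − 0.025^(1/30) = 11.6%
- n = 60: 1 − 0.025^(1/60) = 6.0%
- n = 90: 1 − 0.025^(1/90) = 4.0%

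The one-sided 95% version, 1 − 0.05^(1/n), gives 9.5% for n = 30 and 4.9% for n = 60.

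The documents give no event rate, so a range is assumed. The chance of seeing at least one event is 1 − (1 − p)^n:

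| Assumed true rate p | 30 men | 60 men |
|---|---|---|
| 2% | 45.5% | 70.2% |
| 5% | 78.5% | 95.4% |
| 10% | 95.8% | 99.8% |

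To illustrate precision, 3 events in 60 exposed men is 5.0% (exact 95% CI 1.0% to 13.9%), against 0 in 30 unexposed men (0% to 11.6%). The intervals overlap heavily, so the table describes and does not test. For milder symptoms, the bounds hold only if every participant is asked.

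**The case against.** The strongest reply is that the article declines only *formal* monitoring. It nowhere says that stops or referrals will go unlogged, and a table of discontinuations by arm is the kind of detail a condensed article leaves to the full protocol. This stands in part. The absence of a count by arm is inferred from the article's silence. The decision against formal monitoring, and the reason given for it, are printed and are not silence.

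A second reply is that harm-related data are collected: affect ratings, the fear item, and relationship scales followed to 3 months. This also stands. A reader might infer that the trial will learn nothing about harm, and the article does not support that. These measures would show immediate reactions and relational deterioration by condition, though not adverse events.

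A third reply is that there is no contradiction. A stopping rule for one session is compatible with judging the trial minimal-risk, and protections exist: exclusion criteria, a 10-couple pilot, clinical psychologists on the team, weekly meetings, debriefing and ethics approval. That is correct. These measures lower or manage risk, but nothing in the article says they produce a record of it.

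Finally, a table this small cannot settle whether risk is minimal. That is granted, and it is why only description is proposed.

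**Conclusion.** The point holds as a criticism of a stated design choice. The article declines formal adverse event monitoring for a reason that does not address the harms it foresees, and it states no tabulation of them by arm. The change should be made, but it is not critical: sample size, power, alpha and the primary estimate are unaffected.

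The gain is limited but real. Zero events would bound the rate at 11.6% in one arm of 30 men and 6.0% in the 60 exposed men, given complete logging. At an assumed 5% rate, at least one event would be expected to appear among the exposed men with probability 95.4%.

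Two stronger readings should not be drawn. One is that participants are left unprotected or that a monitoring committee is needed. The stopping, support and referral provisions answer the first, and nothing in the article requires the second. The other is that recorded stop reasons would repair the missing-data analysis. Participants may stop without giving a reason, and outcomes may still be collected after a stop, so any help there is small.

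**What to change.** Replace the sentence in Ethical Considerations with:

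*For both partners, every stopped session (classified as cybersickness, distress, technical failure, other, or no reason given), every spontaneous distress report and every support referral will be logged and tabulated descriptively by arm, separately for men and women, with exact 95% CIs. Negative changes named in the Change Interviews will be listed by arm without CIs.*

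The classification is needed because a technical failure is not a harm. Men and women are kept apart because partners are not independent and their exposures differ. Interview mentions get no CIs because a semistructured interview does not ascertain events in a standard way.

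Optionally, add one brief question on cybersickness and distress, put to everyone at the end of the session, including after a stop. Only this would make the bounds apply to milder symptoms.

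The cost is a short log, one table and a simple listing from interviews already planned, plus one question per person if the option is taken. The intervals will be wide. Recruitment had not begun as of January 2026, and the log should be in place before the first session, since unrecorded stop reasons may not be recoverable.

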## Results

As of January 2026, the trial has not started recruiting participants. Ethical approval has been obtained (approval code CE23-PF02), and the intervention materials and procedures are finalized for implementation. Recruitment and data collection are planned from March 2026 to March 2027, with primary endpoint assessments conducted immediately postintervention and at 3-month follow-up. The first results are expected after completion of follow-up assessments.

## Discussion

### Principal Findings

This study aims to evaluate the potential of IVR as a tool for influencing beliefs related to sexual aggression and associated psychosocial mechanisms among heterosexual men. The REVISE intervention is designed to simulate harassment scenarios from a first-person perspective through partner identity exchange, allowing participants to experience situations from the perspective of their partner. It is expected that this embodied perspective-taking experience will lead to reductions in beliefs that legitimize or minimize sexual aggression, as measured by the AMMSA scale. Additionally, changes may be observed in related psychosocial constructs such as empathy, gender role attitudes, and relationship functioning.

It is expected that the intervention will produce stronger effects in the condition involving partner identity exchange combined with exposure to a harassment scenario, as this condition maximizes embodied perspective-taking. More moderate effects may emerge in the identity exchange condition without harassment exposure, particularly for relational variables such as empathy and partner-related outcomes. In contrast, the third-person observation condition may produce more limited changes because participants do not experience the scenario through an embodied perspective.

Previous research has suggested that IVR can facilitate perspective-taking and emotional engagement by placing individuals in simulated environments that resemble real-world social situations [17-19]. Experimental studies have shown that embodying a virtual avatar from a first-person perspective can influence empathy, bias reduction, and attitudes toward others [20,30]. However, relatively few studies have explored the potential of immersive VR interventions for addressing attitudes associated with sexual harassment and gender-based violence, particularly within dyadic contexts. By incorporating partner identity exchange and relational interaction within the virtual scenario, the REVISE intervention extends prior work by exploring how relational dynamics may influence perspective-taking processes and attitude change [30,31].

### Strengths and Limitations

This study has several strengths. First, it employs a randomized controlled design with 3 experimental conditions, allowing differentiation between the effects of embodiment and exposure to harassment-related content. Second, the study integrates multiple sources of data, including self-report measures, physiological indicators, and qualitative interviews, providing a multimodal assessment of the intervention’s effects. Third, the dyadic design allows examination of relational processes that may shape responses to simulated harassment scenarios.

At the same time, several limitations should be acknowledged. The study focuses on short-term changes in beliefs and attitudes rather than direct behavioral outcomes. Although these constructs are theoretically linked to behavioral responses, the trial cannot directly demonstrate reductions in harassment behaviors in the general population. Furthermore, since the primary outcomes are based on self-reported empathy and attitudes, the results should be interpreted as changes in psychological predispositions rather than observed behavioral conduct. Additionally, the sample consists of heterosexual couples recruited from the general population, which may limit the generalizability of the findings to other populations or relationship structures. Regarding the female participants, their involvement is crucial for the ecological validity of the dyadic interaction. The study design minimizes participant burden by using noninvasive measures, and potential distress is mitigated through strict exclusion criteria for couples in high-conflict relationships and the provision of psychological debriefing if needed. Finally, the intervention involves a single VR session, and longer-term behavioral effects cannot be assumed.

### Future Directions

If the intervention demonstrates promising effects on beliefs and attitudes related to sexual aggression, future research may explore the adaptation of similar VR-based tools for broader educational and prevention programs. Further studies could also investigate the application of immersive perspective-taking interventions in different populations, including educational settings, bystander intervention programs, or rehabilitation contexts.

## Appendix

Multimedia Appendix 1 Peer-reviewer report from Proyectos de Generación de Conocimiento 2022, Ministerio de Ciencia e Innovación (Spain).

Multimedia Appendix 2 SPIRIT checklist.

## Abbreviations

AMMSA: Acceptance of Modern Myths About Sexual Aggression Scale
CPQ: Communication Patterns Questionnaire
IVR: immersive virtual reality
MICE: multiple imputation by chained equations
REVISE: Realidad Virtual Inmersiva y Sexualidad
SAM: Self-Assessment Manikin
VAW: violence against women
VR: virtual reality
